## Methods

### Aims

The primary aim of this study is to assess the feasibility and acceptability of M-PSP. Specifically, the team will evaluate the mobile app–based program in terms of user satisfaction, perceived use of the program, and engagement with the program. A secondary aim of the study is to look for any associations between program completion and engagement with mental health symptoms.

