### Participants

The study is currently open to recruitment, with the aim to recruit 50 pregnant or postpartum individuals across all sites. In prior studies, feasibility studies often include a sample size of approximately 50 participants, which is deemed appropriate to ensure robust findings and comprehensive insights into app usability and effectiveness, balancing the need for inclusivity and accurate representation while accounting for potential participant attrition in digital mediums [14,15]. The inclusion criteria for study participation include (1) aged 18 years or older; (2) pregnant or up to 12 months post partum; (3) scoring 8-16 on the Edinburgh Postnatal Depression Scale (EPDS) [16] or 5-14 on the Generalized Anxiety Disorder-7 Scale (GAD-7) [17]; (4) able to read and speak English; (5) have access to a smartphone or mobile device capable of receiving SMS pushes and supporting Qualtrics Surveys and App (Weill Cornell Medicine); and (6) available to speak by phone or secure videoconference. The exclusion criteria include (2) safety concerns at the time of enrollment; (2) current substance use disorder; (3) current symptoms of psychosis or mania; and (4) history of bipolar or psychotic disorder.

M-PSP is designed to address mild-to-moderate anxiety and depression symptoms and may not be appropriate for more severely impaired individuals. In order to secure feedback from participants matching the app’s target population, the inclusion criteria include those scoring in the mild-to-moderate range on anxiety and depression ratings. Participants with safety concerns at the time of intake, including recent suicidal ideation or self-harm, are excluded as they are at higher risk for heightened symptoms and risk in the perinatal period. Eligibility is not impacted by receipt of clinical care outside of the study, and participants are not excluded if they are receiving concurrent treatment for depression or anxiety.

Study participants may be disenrolled from the study if they are nonresponsive to 16 outreach attempts across 4 consecutive weeks or if their pregnancy ends.

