#### Perinatal-Post Traumatic Stress Disorder Questionnaire-II

The Perinatal-Post Traumatic Stress Disorder Questionnaire-II (PPQ-II) [25] is a validated 14-item self-report measure assessing symptoms of trauma among postpartum individuals. Frequency and duration of symptoms are rated on a 5-point Likert scale from 0=not at all to 4=often for more than a month, with total scores ranging from 0 to 56. Scores of 19 above indicate a clinical range of symptoms that would benefit from additional support. Komurcu Akik and Durak Batigun [25] found that the PPQ-II demonstrates validity and reliability as a scale for assessing the perinatal post-traumatic stress symptoms experienced by mothers.

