### Procedure

As of October 2024, the study is open to recruitment. Recruitment strategies involve advertisements through listservs, clinician information sessions, and flyers within inpatient and outpatient departments. Interested individuals can complete a digital contact information form via a Health Insurance Portability and Accountability Act–compliant survey platform or have their providers complete the contact forms on their behalf.

Study staff reach out to individuals who have completed the form to screen for eligibility. Eligible participants are given further details about study involvement and complete informed consent. Study staff help participants download the app and provide an orientation, with recommendations to use the program for 10 minutes a day, 4 days a week. While it is recommended to complete the program within 6 weeks, sessions can be completed at the participant’s convenience. All participants will be allowed up to 18 weeks for completion in order to account for delays or interruptions that may have occurred during pregnancy or after labor and delivery. Within 1 week of the study orientation, the research assistant will conduct a brief 5-minute phone check-in using a scripted protocol to ensure participants have been able to access and start the app, check on potential technical issues, and answer any questions related to app navigation.

Throughout participation, participants will be able to complete up to 2 sessions per week and will complete the in-app feedback surveys after each session. They will also be sent a text to their phone with a link to complete the daily PST. Additional assessments occur at midpoint (following completion of session 6), post (completion of session 12), and follow-up (6 weeks after post). These assessments include the staff-led feedback interviews via phone or videoconference, as well as the uMARS and all symptom measures. When risk items are endorsed on the daily PST, symptom measures, or during the assessments, study staff are notified and the participant is contacted by a licensed provider to conduct a formal risk assessment and safety plan as necessary.

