### Data Analysis Plan

To analyze qualitative data from the feedback interviews, the grounded theory approach [31] will be used to review all responses and develop a consensus on existing themes. The data will then be systematically coded using these themes in order to identify core concepts and response patterns to derive meaningful interpretations of the feedback.

Data passively collected from the app will be transformed into practical means and ranges that will be used to understand user engagement and program feasibility. Means and SDs will be computed for demographic information and relevant symptom and acceptability questionnaires. Continuous scores from symptom scales and acceptability questionnaires will be analyzed in relation to app use and engagement. Correlations between these variables with be assessed using either Pearson or Spearman correlation depending on data distribution. For example, we will examine the correlation between EPDS symptom scores and app completion rates to explore whether postpartum depression symptoms are related to program feasibility. Hypothesis testing will be conducted with a *P* value=.05 as the threshold for statistical significance, and clinical significance will be considered for correlations that meet a meaningful cutoff (eg, 0.6 or 0.8). This analysis will help identify any demographic characteristics or symptoms that may require greater attention in future iterations of the program to ensure its effectiveness for a broad range of perinatal individuals. For participants who dropped out before study completion, all available data will be included, and any missing data will be handled using simple imputation. A correlation matrix will be generated to explore the relationships between symptom scales (eg, EPDS and GAD-7) and app engagement variables (eg, frequency of use, duration of use), allowing us to investigate possible associations without the need to correct for multiple testing in this exploratory pilot study.

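### Simple imputation of midpoint, post and follow-up symptom scores lets the fill-in rule largely decide their correlation with program completion; correlations with intake scores are unaffected

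*Protocol article*

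**What the plan says.** The Aims section states: "A secondary aim of the study is to look for any associations between program completion and engagement with mental health symptoms". The Data Analysis Plan gives an example: "we will examine the correlation between EPDS symptom scores and app completion rates". It does not say which assessment the EPDS score comes from. It tests correlations at P=.05 without multiplicity correction and also names frequency and duration of use as engagement variables.

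On timing, Procedure says: "Additional assessments occur at midpoint (following completion of session 6), post (completion of session 12), and follow-up (6 weeks after post". These visits include the interviews "as well as the uMARS and all symptom measures". Table 2 also schedules symptom measures at intake, before any app session, and a daily symptom tracker during the study.

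For participants who dropped out, the Data Analysis Plan says "all available data will be included, and any missing data will be handled using simple imputation". It does not name the type of imputation.

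**The concern.** Someone who stops before session 6 has no midpoint score. Someone who stops before session 12 has no post score and, because follow-up is dated from post, no follow-up score. Missingness in these scores is thus a direct function of sessions completed, one of the two variables to be correlated.

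Among observed post scores, sessions completed is always 12, so the observed data say nothing about how post score varies with sessions. Any correlation computed after a single-value fill comes from the fill. Depending on the unnamed rule, it could hide a real association, produce one that does not exist, or reverse its sign. The plan intends to use these correlations to identify symptoms needing more attention in later versions of the program.

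**Working it through.** The protocol derives no figure on this point, so there is none to reproduce. The check has three parts.

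**Inputs.** From the protocol: planned n=50, alpha .05 (taken as two-sided), and assessments triggered by sessions 6 and 12. Assumed, because the protocol gives no values: completion of all 12 sessions 35%, 50% or 75%; average EPDS fall in everyone 0 to 5 points; EPDS means, SDs and correlations as stated below. At n=50 the critical |r| is 2.011/√(48 + 2.011²) = 0.279.

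**1. Mean fill (algebra).** Let S be sessions completed, Y the post score and M the completers' mean post score. After the fill, the overall mean of Y is also M. The sum of cross-products is

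Σ(S − S̄)(Y − M) = (12 − S̄) × Σ over completers (Y − M) + Σ over non-completers (S − S̄)(M − M) = 0 + 0.

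The Pearson correlation is exactly 0 whatever the truth. Spearman's is not exactly 0 in each sample but averages about 0. In simulation, complete-data correlations of -0.44, -0.53 and -0.55 (75%, 50%, 35% completion) all became 0.00. Single regression imputation on intake score also gave about 0.00.

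Frequency of use still varies among completers, so there the effect is attenuation: about -0.48 became -0.24, -0.14 and -0.09. Part of that loss is restricted range and not the fill, since completers alone gave about -0.33, -0.25 and -0.21.

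**2. Carry-forward (closed form).** Take 50% completion, non-completers spread evenly over 0-11 sessions (mean 5.5), intake and post SD 3, no true association, a 3-point fall in everyone, and intake carried forward for every non-completer.

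- Cov(S, Y) = -0.5 × 0.5 × (12 - 5.5) × 3 = -4.875
- Var(S) = 0.25 × 6.5² + 0.5 × (12² - 1)/12 = 10.56 + 5.96 = 16.52
- Var(Y) = 9 + 0.25 × 3² = 11.25
- r = -4.875/√(16.52 × 11.25) = -0.36

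This already exceeds the critical 0.279, although no association exists.

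**3. Carry-forward (simulation, no true association).** Model: intake EPDS normal (12, SD 2.6) clipped to 8-16; post = 12 - fall + 0.5 × (intake - 12) + normal error with SD 3.5; non-completers uniform on 0-11 sessions; Spearman.

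| Average fall | What is carried forward | P<.05 |
|---|---|---|
| 3 points | intake score | 70-82% at 35-75% completion |
| 3 points | last value, midpoint half-improved | 54-72% at 35-75% completion |
| 3 points | last value, midpoint fully improved | 56% at 50% and 31% at 75% completion |
| 2 points | intake score | 41-51% |
| 1 point | intake score | 12-15% |
| 0 | intake score | about 3-6% |

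Repeat runs moved these rates by a few percentage points. A second model (intake mean 12, SD 3, intake-post correlation 0.5, Pearson) gave 58%, 75% and 70% at 75%, 50% and 35% completion for a 3-point fall. In that model, a true positive correlation of +0.44 to +0.55 came out as -0.14 to -0.21.

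**The case against.** The strongest reply is that the EPDS example may mean the intake score. The plan says that the analysis asks whether symptoms are related to feasibility and which symptoms need attention, which reads naturally as symptoms predicting completion. Intake scores precede any session, so those correlations are untouched. This stands, and it limits the point to post-intake scores. A reader might infer that the whole secondary aim is decided by the imputation; the text does not support that. It names no time point for the EPDS example, but neither does it restrict the imputation rule to intake data.

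Second, exact zero applies only to session count against post or follow-up scores. Midpoint scores exist for anyone with 6 to 12 sessions, usage frequency and duration vary among completers, and the daily tracker does not depend on sessions. This also stands.

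Third, the protocol names no carry-forward, and the size depends on assumed completion and score change. That is true, and ranges are shown for that reason. But the common simple rules examined either erase the association or, when scores fall on average, create one.

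Fourth, Table 2 uses week columns, which might suggest calendar-based visits. Procedure, however, defines midpoint and post by session completion and states no assessment for people who stop early.

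Fifth, the aim is exploratory, carries no hypotheses and is unpowered. That excuses imprecision, not a result set by the fill-in rule, but it does lower the severity.

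**Conclusion.** The concern holds for midpoint, post and follow-up symptom scores. The protocol fixes a rule under which their correlation with program completion largely reflects how gaps are filled. Mean fill gives exactly 0 for sessions against post score (Pearson) and attenuates correlations with frequency of use. Carry-forward gives P<.05 in about 54-82% of trials with no true association, assuming a 3-point average fall and 35-75% completion. The rate is lower if midpoint scores have already improved fully, and about nominal if scores do not fall on average. The distortion needs some non-completers and, for carry-forward, some average change.

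Three further inferences are tempting but unsupported. The text does not say that PPQ-II will be imputed for participants who are still pregnant: the imputation sentence concerns dropouts. It plans means, SDs and correlations, so a claim about confidence intervals being too narrow has no planned interval to attach to. And multiple imputation with sessions completed as a predictor of post score is no cure, because that predictor is constant at 12 wherever post is observed.

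This should be fixed but is not critical: the progression criteria in the Discussion rest on retention from screening to enrollment and on completion of primary measures, not on these correlations.

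**What to change.** In the Data Analysis Plan:

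- Delete simple imputation for symptom scores.
- State that completion and engagement are correlated with intake EPDS and GAD-7, which are collected before any session.
- Analyse later symptom scores without single-value fill, using a mixed model on all observed visits (intake, midpoint, post, follow-up).
- State that the relation of sessions completed to post or follow-up scores cannot be estimated from these data, because everyone with such a score completed 12 sessions.
- Report missing uMARS as nonresponse.

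The cost is analysis wording and modest extra modelling, with fewer observations and wider uncertainty for post-intake associations. No data collection changes, and analysis is planned only after the last participant finishes, so there is time to make the change. Estimating the sessions-by-post-score relation itself would need assessments at fixed times regardless of sessions completed, which is a design matter for a later study.

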### Ethical Considerations

The study was granted approval through the Biomedical Research Alliance of New York IRB (BRANY #23-02-134-380) and the internal IRB within the academic medical center at which the trial is being conducted. The study has been registered at ClinicalTrials.gov (protocol number NCT05897619). This protocol was written in accordance with the SPIRIT (Standard Protocol Items: Recommendations for Interventional Trials) guidelines (Multimedia Appendix 2) [32]. All participants provided informed consent and were made aware that they could withdraw from the study at any time without penalty. Participants are not compensated for their participation. All participants may continue to use the MAYA app following study completion if they so choose and will be given a list of resources, including referrals for clinical care.

While no individual data will be reported, the study team will report results via publication following trial completion. Health care providers within the Weill Cornell Medicine or NewYork-Presbyterian network may be given access to a summary of qualitative and quantitative outcomes. Every participant is given a unique study identifier. All data collected were confidential and safely stored per protocol approved by the IRB. As a small, unblinded study that does not involve invasive procedures or greater than minimal risk, there is no data monitoring committee. The study is internally sponsored, with no external funding organization involved in study design, management, monitoring, or analysis. The study is fully monitored by internal co-investigators, with IRB oversight through BRANY**.**

## Results

The pilot trial received internal funding in August 2023 and data collection started in September 2023. As of October 2024, 32 participants have been enrolled in the study. It is anticipated that enrollment will continue throughout 2024, with projected recruitment completion in December 2024. Data analysis will be completed upon study completion of the last participant.

## Discussion

This study aims to assess the feasibility, usability, and acceptability of the M-PSP, a 12-session program teaching skills derived from CBT and adapted to suit the unique needs of a perinatal population. Regarding feasibility, it is anticipated that outcomes will indicate the program is able to be worked through by users, but that pacing and session length may need more flexibility in future versions of the app to account for the particular demands of this population. It is hypothesized that users will find the skills to be acceptable, but that some of the sample videos need revision to more directly reflect mood and anxiety concerns during and after pregnancy. Further, the study team anticipates that users will have input on specific content that could be added to improve their satisfaction with the app. Regarding usability, it is anticipated that the app will be user-friendly and easy to work through. As the secondary aims are exploratory, there are no specific hypotheses related to symptom measures as they are related to engagement. These outcomes will inform future iterations of the program in hopes of developing a widely accessible and useful tool for pregnant and postpartum individuals.

While the findings from this pilot study will provide valuable insights, several limitations must be acknowledged. This study relies on self-report data, which may introduce biases such as social desirability or recall errors. In future studies, clinician assessment of symptoms could help to mitigate these concerns. In this and future studies, the use of passively collected app usage data should provide some objective metrics regarding engagement and feasibility. A further limitation is the small sample size. As a pilot trial, this study is not powered to detect statistical significance, as the primary aim is to assess feasibility and acceptability rather than efficacy. Therefore, these findings should be interpreted as preliminary, and further research with larger samples will be necessary to assess the program’s effectiveness in improving mental health outcomes.

Despite these limitations, this study is an important step in helping to fill the gap between an increasing maternal mental health crisis and barriers to appropriate support. By using a community-based-participatory research model, the development team has been able to consider input from researchers and clinicians across different specialties and will be able to incorporate feedback from end users through each stage of program development. Once feedback has been considered and incorporated into the program, the team will look to conduct future studies to assess the effectiveness of the tool in helping perinatal individuals manage anxiety and mood symptoms. Per guidelines on progressing from a pilot trial to a fully powered randomized controlled trial (RCT) [33], the research team has outlined a number of criteria that will influence the next steps. To ensure adequate participant numbers for an RCT, the pilot trial will need to demonstrate a 50% retention rate between screening and enrollment. The team will also move forward if 75% of participants complete primary outcome measures, which consist of feasibility, acceptability, and usability feedback interviews and surveys. While the study team will track adherence to the intervention (ie, completing M-PSP sessions), this will not be used as a criterion for progressing to a full RCT as nonadherence may be attributable to feasibility or acceptability concerns that the pilot study intends to illuminate so that future versions of the app can be modified prior to an RCT.

## Appendix

Multimedia Appendix 1 Sample screenshots of the MAYA Perinatal Skills Program.

Multimedia Appendix 2 SPIRIT (Standard Protocol Items: Recommendations for Interventional Trials) checklist.

## Abbreviations

CBT: cognitive behavioral therapy
EPDS: Edinburgh Postnatal Depression Scale
GAD-7: Generalized Anxiety Disorder-7 Scale
IRB: institutional review board
M-CBT: Maya-Cognitive Behavioral Skills Program
M-PSP: Maya-Perinatal Skills Program
PHQ-9: Patient Health Questionnaire-9
PMAD: perinatal mood and anxiety disorder
PPQ-II: Perinatal-Post Traumatic Stress Disorder Questionnaire-II
PST: pregnancy symptom tracker
RCT: randomized controlled trial
SPIRIT: Standard Protocol Items: Recommendations for Interventional Trials
uMARS: user version of the Mobile Application Rating Scale
